### Data collection

Three main types of data will be collected: Pre and post implementation point prevalence and patient demographics (quantitative) Pre and post implementation clinician knowledge and competence (quantitative) Post implementation perceived barriers and enablers to implementation (qualitative)

Data collection types and details are outlined in Table 2, and the data collection timepoints are displayed in Fig. 1.

**Table 2 Tab2:** Data collection sources and methods

Data	Data collection method	Data source(s)	Data collected	Data collection timepoint(s)
IDC usage rate and incidence of CAUTI	Online data collection tool	- Patient medical records – facility-wide across all four hospitals - Bedside observation - Infection control database	- Urinary catheter presence - Days catheter in situ - CAUTI rate	- Baseline - 4 months post-implementation commencement - 9 months post-implementation commencement
Patient profile	Data extraction and then merge with data from point prevalence	- Electronic patient management systems	- Patient demographics including age, gender, weight, diagnosis, type of admission	- Baseline - 4 months post-implementation commencement - 9 months post-implementation commencement
Clinician knowledge and competency	Online survey	- Clinicians (all nurses and medical officers invited from participating hospitals)	- Clinician competency - Clinician knowledge of CAUTI prevention - Perception of unit-based culture	- Baseline - 6 months post-implementation commencement
Barriers and enablers to implementation	Focus group	- Clinicians (6–8 per facility) (all nurses and medical officers invited from participating hospitals)	- Perceived barriers and enablers to implementation	- 6 months post-implementation commencement

The point prevalence data will be collected by project staff (clinical nurse consultants, research assistant), nurse and midwife clinicians and clinical nurse educators from each hospital. Training will be administered to all clinicians involved on data collection techniques and definitions prior to collection, and they will be paired where possible with members of the research team. Data collection staff will go to every inpatient bed on every adult inpatient ward in the hospital and input data into a firewall protected online survey tool. Survey data will then be exported and merged with other electronically extracted demographic patient data into statistical package STATA [38] for analysis.

### Exclusion and inclusion criteria

Point prevalence data will be collected from all adult inpatient wards across four hospitals in two Health Districts (excluding emergency departments, operating theatres and day only wards).

### Multifaceted intervention

The intervention will be delivered in all adult inpatient wards, emergency departments, and operating theatres in all four hospitals. The key component of the intervention is the evidence-based “No CAUTI” bundle (Table 3). To support implementation of the No CAUTI bundle, the following resources were developed as part of the intervention:

**Table 3 Tab3:** Evidence base for No CAUTI Bundle

N	NEED for catheter assessed – refer to indications, scan bladder, consider alternative, document indication. - Need for IUC is assessed - appropriate indications for insertion [7, 47, 48]. - Scan the bladder to determine bladder volume [7] - Consider alternatives such as external sheath (males),intermittent catheterisation by staff/patient, SPC, double voiding, commode, timed toileting [7, 47, 48]
O	OBTAIN patient consent, OFFER patient education including hygiene. - Obtain patient consent and importance of accurate complete documentation. - Provide written and verbal information to patient/carer [49] - Ensure daily meatal hygiene is performed as part of personal hygiene, soap and water is all that is required [7, 47, 48]
C	COMPETENCY – clinicians who insert catheters must have documented competency - Competent and trained staff should insert catheters [7, 48]
A	ASEPSIS – maintain asepsis & hand hygiene during insertion and while catheter is in place. - Aseptic technique and sterile equipment must be used for IUC insertion. Hand hygiene “Moment 2” and non-sterile gloves is recommended when manipulation of the IUC or drainage system is required. - Empty the bag when ¾ full and use a clean container for each patient; avoid contact between outlet and container. - Maintain a sterile closed system of drainage [7, 48]
U	UNOBSTRUCTED flow – no kinks or loops, catheter secured, bag below bladder level and off the floor. - Unobstructed continuous urine flow with no kinks or loops, bag below the bladder and not in touch with any surface. Secure the catheter to the patient to minimise movement and trauma and improve patient comfort [7, 48]
T	TIMELY catheter removal and documentation – may be nurse initiated. - Timely removal of the IUC - daily review. Nurse initiated removal guidelines followed if there is no medical documentation for continued use [7, 48]
I	INFECTION risk – daily periurethral hygiene. Collect urine specimen only when clinically indicated. - Infection and catheter specimen urine (CSU) collection: must be collected using aseptic technique, from a newly inserted catheter and before the commencement of antimicrobials - CSU should only be collected if clinically indicated [7, 47, 48]

 IDC insertion criteria guidelines Indications for IDC specimen collection Nurse-led IDC removal guidelines (Additional file 1) Educational resources and compliance auditing tools

The distribution and standardised use of a cost-effective, generic IDC insertion pack forms part of the intervention. The insertion pack includes all equipment required for catheterisation, documentation stickers, and securing devices.

Routine assessment of clinician competency in urinary catheter insertion will be introduced as part of the multifaceted intervention.

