## Methods/Design

### Aims

The primary aim of the study is to reduce IDC usage rates by reducing inappropriate urinary catheterisation and duration of catheterisation.

The secondary aims of the study are to identify:The current inpatient indwelling urinary catheter usage rate and incidence of CAUTI;If the implementation and adherence to bundled catheter care (BCC) reduces IDC use and CAUTI;How effective BCC is in improving IDC-related outcomes;The barriers and enablers to successful implementation of BCC; andThe cost benefits of implementation.

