**Fig. 1 Fig1:**
[figure not shown]
Study Design. Data collection points are indicated with diamonds on timeline

Implementation of the intervention across four acute care hospitals will be staged, with multiple clusters in each of two implementation stages. Pre and post point prevalence data comparison will occur within all hospitals pre and post intervention, as well as between the two Health Districts as detailed in Fig. 1.

The staged implementation of the intervention allows for a control between the two Health Districts.

A mixed method design provides a platform to explore in-depth existing barriers and enablers related to implementing practice change. The sequential phased nature of the study ensures that the necessary evidence is available to inform the subsequent implementation phase of the study. The focus groups will identify barriers and enablers to implementation and uptake and will inform strategies to embed the intervention into normal practice. Questions in the focus groups will be informed by results from the point prevalence and clinician surveys.

The control will be usual urinary catheterisation practice, i.e., no intervention or implementation strategies. NSW Health evidence-based practice guidelines for “Adult Urethral Catheterisation for Acute Care Settings” [35], and local clinical practice guidelines for urinary catheterisation for each Health District are available for all clinicians, and can be accessed online.

The Clinical Excellence Commission (CEC), a corporation addressing patient safety and clinical quality in the NSW Health context, established a CAUTI project in 2014 to “help healthcare professionals in reducing the incidence of CAUTIs in acute care settings” [36]. A urinary catheterisation course on an online NSW Health learning platform also exists [37].

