### Economic evaluation

The economic evaluation will be based on a cost-effectiveness analysis to determine whether the multifaceted care intervention is more cost-effective than usual care in reducing CAUTI amongst hospital inpatients. A healthcare provider perspective will be adopted. International guidelines for conducting economic evaluations, as recommended by Drummond et al.[45], and Husereau et al. [46] will be followed. Resource use will be identified using a short data collection instrument. Cost related data collected from usual care and intervention arms will include: materials used for catheterisation, proportion of patients receiving IDC, CAUTI rates, LoS for patients diagnosed with CAUTI, and CAUTI treatment expenses (e.g. antibiotics).

The measure of effect will be based on the change in the rate of CAUTI between the usual care and intervention groups. If the expected intervention benefit is demonstrated in the trial, the measure of effect will be the cases of CAUTI avoided due to the intervention. The economic analysis will identify the cost to avoid an additional case of CAUTI. The reportable outcomes will be average cost-effectiveness and incremental cost-effectiveness ratios. A sensitivity analysis will be conducted to explore the robustness of the results to the uncertainty around parameters used in the model. The results will be interpreted in a broader decision making framework that includes acceptability and sustainability of the intervention. The economic sustainability of the intervention will be based on the cost and effect of delivering the intervention in a wider setting. The analysis will also report the resources required to implement the intervention in other localities. This information is relevant to policy makers because it reflects the resources required by other Health Districts to implement the intervention.

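### The bundle changes when and how urine specimens are taken while CAUTI is counted from routine records, so the CAUTI comparison and the cost per CAUTI avoided are open to detection bias of unknown size

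*Protocol article*

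**What the plan says.** **The intervention.** Under Multifaceted intervention, the infection-risk element of Table 3 instructs staff: "Collect urine specimen only when clinically indicated". For catheter specimens it repeats that "CSU should only be collected if clinically indicated" and adds that they "must be collected using aseptic technique, from a newly inserted catheter and before the commencement of antimicrobials". One of the supporting resources developed for the bundle is "Indications for IDC specimen collection".

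**The comparator.** The Design section says: "The control will be usual urinary catheterisation practice, i.e., no intervention or implementation strategies". It also notes that state and local catheterisation guidelines are available to all clinicians. What those say about specimens is not given.

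**The outcome.** Table 2 (Data collection) takes IDC usage and CAUTI from medical records, bedside observation and the "Infection control database". The statistical analysis section adds data linkage for CAUTI rates. Number of specimens sent is not among the items collected.

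**The use of the outcome.** One secondary aim is to find out "If the implementation and adherence to bundled catheter care (BCC) reduces IDC use and CAUTI". The Economic evaluation section says: "The measure of effect will be based on the change in the rate of CAUTI between the usual care and intervention groups". It then reports the cost of avoiding one further case.

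**The concern.** A recorded CAUTI from routine sources can depend on whether a specimen was sent and how it was taken. The bundle acts on both, and it does so when the intervention starts and only where it has started. The pre-post contrast and the contrast between Health District 1 after implementation and the untreated Health District 2 would then compare two testing regimes as well as two levels of catheter care.

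The safeguards in the plan are aimed at other problems. The staged control deals with secular trends, ward stratification with case mix, and baseline adjustment with patient demographics. None of them removes a detection change that is itself part of the intervention.

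At stake are the secondary CAUTI conclusion and the economic result, where a case that is no longer recorded would count as a case avoided.

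**Working it through.** **1. The plan's own figure.** The article gives one sample size, 500 per Health District for a fall from 15% to 9% in IDC rates (power 0.8, alpha 0.05). The two-sided two-proportion formula is

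n = [1.96·√(2·0.12·0.88) + 0.842·√(0.15·0.85 + 0.09·0.91)]² / 0.06²

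This gives 460, or 493 with continuity correction, so 500 reproduces. It concerns catheter use. The article gives no design figure for CAUTI, and the present point disputes no stated number.

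**2. Is the testing change tied to the intervention?**
- Changed specimens: stated directly (aseptic technique, new catheter, before antimicrobials).
- Fewer specimens: the natural effect of an only-if-indicated rule, but inferred, because specimen practice under existing guidelines is not shown.
- Control: receives neither the bundle nor its resources.
- Ascertainment: records, infection control database and linkage. Bedside observation is listed too, but it can show a catheter and cannot supply a culture. The article describes no study-mandated specimen.

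**3. How large could the effect be?** Let a be the share of recorded cases that are positive cultures without infection, and c the fraction of those that the specimen rule removes. With true infection unchanged:

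relative fall in recorded CAUTI = a × c

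Neither a nor c is in the documents, so the values below are assumptions.

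| a | c | Fall in recorded CAUTI |
|---|---|---|
| 0 | any | 0% |
| 0.10 | 0.50 | 5% |
| 0.25 | 0.50 | 12.5% |
| 0.50 | 0.50 | 25% |
| 0.50 | 0.75 | 37.5% |

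**4. In cases.** The Background cites CAUTI at 0.9% (six-hospital survey) and 2.2% (two-ward pilot prevalence study). Treating every bed in Table 1 as one surveyed patient:
- Health District 1: 620 × 0.009 = 5.6 to 620 × 0.022 = 13.6 cases per survey.
- Health District 2: 867 × 0.009 = 7.8 to 867 × 0.022 = 19.1 cases per survey.

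A 25% artefact in Health District 1 is 0.25 × 5.6 = 1.4 to 0.25 × 13.6 = 3.4 cases, so a few unsent specimens could alter the result. Per 1,000 inpatients it is 1,000 × 0.009 × 0.25 = 2.25 to 1,000 × 0.022 × 0.25 = 5.5 apparent cases avoided.

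**5. When there is also a real effect.** Let true infections fall by r and leave culture-only cases otherwise unchanged. The recorded fall is

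F = (1 − a)·r + a·c

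With r = 0.20 and a = c = 0.5, F = 0.10 + 0.25 = 0.35. At 0.9%, there are 9 recorded cases per 1,000. Apparent cases avoided are 9 × 0.35 = 3.15 and infections avoided are 9 × 0.10 = 0.9. The denominator of the cost-effectiveness ratio would be 3.15 / 0.9 = 3.5 times too large under these assumed values.

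**The case against.** The strongest reply is that everything turns on the CAUTI case definition. The article does not print it, but data collectors are trained on definitions, so one exists. If it requires symptoms, patients with a clinical indication are still sampled under the bundle, a is close to zero and the bias may be small. That stands, and the missing definition is not a fault in a condensed article. It limits the size without closing the issue: if a positive culture is also required, a changed sampling method can still shift the count.

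The direction is also open. Sampling before antimicrobials could raise culture yield. The bundle stresses full documentation, and treated wards are audited weekly and then monthly, either of which could increase recorded CAUTI. A downward bias remains the likelier result of an only-if-indicated rule, but it is not established.

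A reader might go further and infer that the CAUTI and cost objectives cannot be answered, that the bias must favour the intervention, or that recorded CAUTI falls in proportion to specimens sent, by perhaps 20% to 40%. The documents support none of these. An indication filter removes non-indicated specimens first, so proportionality is not a natural model. Nor is the planned 40% effect a yardstick, since it concerns catheter use.

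Finally, the economic section already plans a sensitivity analysis, and some of its inputs (materials, proportion of patients with an IDC) need no specimen. Fewer culture-only diagnoses treated would also save real cost. All true, but the planned analysis addresses parameter uncertainty and does not name a shift in how the effect measure is detected.

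**Conclusion.** The point holds as a risk of detection bias. Two things the article fixes are in tension: the bundle alters specimen collection, and CAUTI is taken from sources that routine care generates. Followed as written, the plan can count a testing change as CAUTI avoided and carry it into the cost per case.

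The size cannot be determined from the documents. Under the assumed ranges it runs from nothing to a 37.5% fall in recorded CAUTI with infection unchanged. The figure rests on a, c, the unprinted case definition and unknown specimen practice under existing guidelines. The direction is likely to be towards fewer recorded cases, but this is not certain.

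The primary aim is unaffected, because IDC presence is recorded by visiting every adult inpatient bed. The change is worth making but is not critical to the trial's main conclusion.

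**What to change.** - **Data collection, Table 2:** add the number of urine specimens sent from catheterised patients, by survey and district. Report specimens per catheterised patient (or per catheter-day) beside each CAUTI rate.
- **Definition:** state that the same CAUTI case definition applies in both periods and both districts.
- **Statistical analysis and Economic evaluation:** add a sensitivity analysis for changed testing. Repeat the CAUTI comparison and the cost-effectiveness ratio (i) restricted to cases with recorded symptoms and (ii) over a range of a × c. For (ii), with baseline recorded rate p and observed relative fall F, infections avoided per patient are p × (F − a × c) under the model above.
- **Interpretation:** describe a fall in CAUTI as infections avoided only together with these results.

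The specimen count should be reported descriptively and not used as a condition. Fewer true infections also produce fewer indicated specimens, so it lies partly on the causal path. Nor should CAUTI be kept out of the economic base case unless a second outcome also falls. At about 6 to 19 cases per district survey, and power of about 11% to 23% for a 40% fall (620 against 867 patients, independence assumed), such a rule would act mostly on noise.

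The cost is a small additional extraction from records already being searched, a few sentences in two sections, and more cautious CAUTI and cost conclusions. Bundle content need not change.

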### No CAUTI Bundle

The “bundled intervention” framework used in this project is defined as a collection of a number of evidence based practices or steps, vital to achieving improvement in clinical outcomes [39]. The “No CAUTI” bundle was developed during the pilot project, and is based on evidence-based recommendations. The evidence for the bundled intervention is presented in Table 3.

### Implementation strategies

A number of implementation strategies will be used in the project: education, monitoring and feedback, resources, and facilitation. The timing of implementation is displayed in Fig. 2. The Template for Intervention Description and Replication (TIDieR) was developed to improve the quality of descriptions of interventions [40], and can be used to report content of behavior change interventions, including what is delivered, who the intervention is delivered to, and what materials are used. TIDieR has previously been used to describe care bundle interventions [41]. The TIDieR framework has been used to outline the current implementation strategies in Table 4.

**Fig. 2 Fig2:**
[figure not shown]
Timeline of implementation components. The intervention commences with four weeks of intensive education. For the first two months, compliance audits are completed on a weekly basis, and then continue on a monthly basis for the remainder of the 6-month intervention period. Champion meetings will be held on a monthly basis throughout the intervention period

**Table 4 Tab4:** “No CAUTI” Implementation strategies summary based on TIDieR

Implementation Strategy	Rationale	Mode of delivery	Delivered by	Delivered to and where	When/how often
Education					
Train-the-trainer workshops	To prepare educators to present the “No CAUTI” bundle to ward-based staff, and to train educators to complete urinary catheterisation competency assessments	Face-to-face (group)	Clinical nurse consultant – urology	Nurse educators from across hospital	1x 2-3 h workshop at each facility at start of intervention
Ward in-services	To familiarise staff with “No CAUTI” bundle and nurse-initiated removal flowchart To identify champions in each ward	Face-to-face (group)	Nurse educators	Nurses and medical officers from all adult inpatient wards, OTs, and EDs	Minimum 1x 20 min in-service in each ward at start of intervention
Monitoring and feedback					
Compliance audits and feedback	To monitor compliance with “No CAUTI” bundle and provide strategies to support implementation	Individual patient audit, and feedback face-to-face (group) to clinicians	Champions (clinicians previously identified in in-services)	All inpatient wards	Weekly for first two months and then monthly for remaining 4 months of intervention period.
Feedback of point prevalence of IDC usage and CAUTI	To focus clinicians on targets and progress	Face-to-face (group) and email	Research project staff	All clinicians at a ward, facility, and district level	Baseline, 4 months, and 9 months
Resources					
“No CAUTI” bundle posters	Prompt awareness and better documentation	Documents displayed in wards	N/A (passive component)	Nurses and medical officers	Ongoing
“No CAUTI” bundle badges	Prompt awareness of intervention and identify ward champions	Worn by clinicians and champions	N/A (passive component)	Nurses and medical officers	Ongoing
Catheter insertion DVDs	Educate nurses about correct catheterisation processes	Available on intranet	N/A (passive component)	Nurses	Ongoing
Facilitation					
Competency assessments	Increase proportion of clinicians that are competent in urinary catheterisation	Face-to-face (individual)	Nurse educators	Nurses	Ongoing
Champions	Act as a resource for clinicians and promote the No CAUTI bundle to clinicians; support implementation	Face-to-face (individual and group)	Nurses	Nurses and medical officers	Ongoing

Whilst there are key implementation strategies that will be common to all intervention hospitals, there will be a degree of flexibility between the two Health Districts, and their hospitals. Both active (e.g. workshops, audit and feedback) and passive strategies (e.g. distribution and display of posters, equipment) will be used [28].

Previous studies have identified champions as playing a significant role in reinforcing practice change [42]. The need for multiple champions when implementing a large degree of practice change is recommended [43]; the current study will have a champion in each ward, and champions will meet regularly. Nursing staff are critical to the success of bundled interventions aimed at reducing IDC use [27].

